## Study Endpoints

**Primary Endpoint**

The primary efficacy endpoint is that the patient is alive and extubated at 48 hours post surfactant administration. We hypothesize that Curosurf® will increase the proportion of infants alive and extubated within 48 hours after surfactant therapy.

**Secondary Endpoints**

The following endpoints will also be measured in this study:

- duration of respiratory support (respiratory support via an endotracheal tube and non-invasive respiratory support)
- duration of NICU stay
- extubation failure rates
- need for additional surfactant doses
- adverse events (during and following administration of surfactant)
- death before discharge
- incidence of pulmonary morbidities up to 36 weeks GA

# Expected Duration of Subject Participation

The duration for each infant in the study will vary according to the gestational age. Follow up is done until the infant is 36 weeks GA or at discharge, whichever is first. All assessments will be done according to the Timetable of Events. These time points are simply for data collection and no extra tests or procedures are done for the purposes of this study, from the perspective of the infant or the parent/LAR.

# Study Medication/Intervention

Infants will be randomized in a 1:1 manner, to receive either the study drug, Curosurf® or the control drug, BLES®. The treatment dose for Curosurf® is 2.5 ml/kg (200mg/kg) for the first dose and 1.25 ml/kg (100mg/kg) for repeat doses. For BLES® the recommended dose is 5 ml/kg. Either drug is given by syringe into the endotracheal tube by a Respiratory Therapist. The SOP for administering both study drugs is found in Appendix E of this protocol.

After consent is obtained, and all inclusion/exclusion criteria are fulfilled an infant can be randomized into the trial. A blinded study RT will administer the drug according to the SOP found in Appendix E (also in the Resource Manual). The RT will document the procedure using the source documents provided by the sponsor and will also complete all Drug Accountability logs, as appropriate. Detailed instructions for completion of drug accountability logs are found in the Resource Manual.

The blinding procedure for administration of both study drugs is as follows:

- As the volume and viscosity of Curosurf® and BLES® are different, blinding of the RT administering the surfactant is not feasible. However, at any given time, two RTs work in the NICU. Doses of surfactant will be prepared away from the bedside by a RT not otherwise involved in the care of the infant. The surfactant will be drawn into a syringe and placed in a covered box. The RT will administer the surfactant with the syringe masked by a large label covering the amount of the contents. The RT will record in the patient’s chart that surfactant was provided but will not include the name or the dose of the product. This RT will not care directly for the infant for at least 48 hours following administration of the surfactant. The clinical and research teams will be blinded to the identity of the assigned surfactant throughout the study, unless an emergency occurs requiring unblinding

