## 6.1 Study Medication Description

Study medication for this trial will be maintained in bulk supply format, the vials will not be individually numbered. For both Curosurf® and BLES®, the correct dose, which is weight based, will be calculated by the study Investigator and the RT will be responsible to double check the calculation. Either study drug is given by endotracheal method within 48 hours of life. Repeated doses may be given, up to a maximum of 3. If further doses are required then open label BLES® should be administered. The doses should not be given more frequently than every 6 hours.

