## 6.3 Formulation, Packaging, and Labeling

Curosurf® is manufactured and provided by Chiesi Farmaceutici S.p.A. A detailed Product Monograph is found in Appendix F. The vials will be labeled for investigational study use. The commercial label will not be present. The vials will be shipped and stored between +2 and +8 degrees Celsius. There are two vial sizes for the study 1.5 mls and 3.0 mls.

The label applied on the vial will contain the following information:

| Curosurf-01  Poractant alfa 80 mg/mL - X mL  Expiration: DD-MMM-YYYY  Store in refrigerator between +2°C and +8°C, protected from light  Lot # -------  Protocol Code: ----------  Sponsor: The Ottawa Hospital, [name]  Investigational drug to be used only by a qualified Investigator | Curosurf-01  Poractant alfa 80 mg/mL - X mL  Expiration: DD-MM-YYYY  Conserver au réfrigérateur entre +2°C et +8°C, à l’abri de la lumière  Lot # -------  Code du Protocole: ------------  Commenditaire: The Ottawa Hospital, [name]  Médicament expérimental à être utilisé seulement par un Investigateur qualifié |
| --- | --- |

BLES® is manufactured by BLES Biochemicals Inc. A detailed Product Monograph is found in Appendix G. A dedicated stock of 3 and 5 ml vials will be secured by the sponsor. The vials will be relabeled using the template as below.

| Curosurf-01  BLES- X mL  Expiration: DD-MMM-YYYY  Store at -20°C for long term and then may be thawed and stored at +2°C to +8°C  Lot # -------  Sponsor: The Ottawa Hospital,  [name]  Investigational drug to be used only by a qualified Investigator | Curosurf-01  BLES- X mL  Expiration: DD-MM-YYYY  Conserver au congélateur à long-terme à -20°C et peut ensuite être dégelé et conservé de nouveau entre +2°C et +8°C  Lot # -------  Commenditaire: The Ottawa Hospital,  [name]  Médicament expérimental à être utilisé seulement par un Investigateur qualifié |
| --- | --- |

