## 6.4 Accountability Procedures and Storage

**Investigational Group-Curosurf**®- Vials will be stored between +2 and +8 degrees Celsius. The study medication will be received by the site pharmacy and a drug receipt form will be completed and sent back to the shipper. A two month supply of drug will be transferred to the NICU where it will be stored in a locked container.

**Control Group-BLES**®- The vials will be stored in a -20 degrees Celsius freezer in the study center Pharmacy. A two month supply will be thawed and kept in the refrigerator in the NICU, in a dedicated locked container, to avoid mixing with regular NICU stock. These will be clearly labeled with an “expires on ____” date, to avoid administering drug that has been at refrigerator temperatures over the allotted time.

For both study drugs temperatures will be monitored daily, both in the main pharmacy and in the NICU, capturing the minimum and maximum temperatures for the previous 24 hours. Detailed instructions for cold chain management are found in the Study Resource Manual.

Drug accountability forms will be completed in the pharmacy for the main stock and subject accountability forms will be completed as each vial is administered in the NICU. Please see the Resource Manual for further instructions for completing the Drug Accountability forms.

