# Data Handling and Record Keeping

## Data Management Responsibilities

Data collection will be the responsibility of the research staff at each site under the supervision of the Principal Investigator and Sub-Investigators. During the study the investigator will maintain complete and accurate documentation for the study.

Data collection for the study will be done using an eCRF (REDCap). Both study centers will enter study information into this system. All information will be de-identified, using a unique subject number for each infant enrolled into the study.

All source documents and lab reports must be reviewed by the clinical team and data entry staff, who will ensure that they are accurate and complete. Adverse events will be graded, assessed by severity and causality and reviewed by the site investigator or designee.

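### The protocol masks only the patient's chart, sets no access limit on dosing and accountability records, and requires blinded staff to review all source documents; these rules need reconciling

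*Protocol*

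**What the plan says.** **The blind.** Section 6 (Study Medication/Intervention) states: "The clinical and research teams will be blinded to the identity of the assigned surfactant throughout the study". The only exception is an emergency that requires unblinding. To protect the blind, doses are prepared away from the bedside, the syringe is masked, and the chart entry leaves out product and dose.

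**The dosing records.** The same section states: "The RT will document the procedure using the source documents provided by the sponsor and will also complete all Drug Accountability logs". On how to fill in the logs it says: "Detailed instructions for completion of drug accountability logs are found in the Resource Manual". Section 6.4 (Accountability Procedures and Storage) adds that "subject accountability forms will be completed as each vial is administered in the NICU". Neither section masks these records or says who may see them.

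**The supply.** Section 6.1 describes bulk stock and says "the vials will not be individually numbered". In Section 6.3 the Curosurf label carries "Poractant alfa 80 mg/mL - X mL", and the control label carries the name BLES.

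**The review rule.** Section 10 (Data Management Responsibilities) states: "All source documents and lab reports must be reviewed by the clinical team and data entry staff". The purpose is accuracy and completeness. No document type is excepted and no time for the review is given.

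**The concern.** The protocol recognises that a written product name or dose would break the blind, because it removes both from the chart. It applies no such rule to the other records that the RT completes. Section 10 then sends all source documents to the people the blind is meant to cover.

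What is at stake is decisions taken with knowledge of the arm. The primary endpoint, alive and extubated at 48 hours, depends on a clinical act, and Appendix B lets physicians extubate from higher settings at their discretion. Redosing (Sections 7.2 and 7.3.1), reintubation, and the site investigator's assessment of causality (Section 10) also involve judgement. Knowledge of the arm could influence any of them.

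**Working it through.** No figure in the protocol is in dispute. The check sets the sections side by side and asks whether the records would identify the arm.

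**1. Which records are masked?**

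| Record | Masking or access rule stated | Reached by the Section 10 review? |
|---|---|---|
| Patient's chart (Section 6) | Product and dose left out | Harmless if it is |
| RT's sponsor source document (Section 6) | None | Yes: Section 10 covers all source documents, and Section 11 also uses that term for the forms the sponsor provides |
| Subject accountability form (Section 6.4) | None | Unclear: Section 6 lists the logs separately from source documents |

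**2. Would volume identify the arm?** Inputs are the Section 6 volumes: Curosurf 2.5 ml/kg first and 1.25 ml/kg repeat; BLES 5 ml/kg.

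- BLES to first Curosurf dose: 5 / 2.5 = 2.0.
- BLES to repeat Curosurf dose: 5 / 1.25 = 4.0.
- At 1 kg: 5 ml against 2.5 ml and 1.25 ml.

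Volume alone does not settle it: 2.5 ml is a BLES dose at 0.5 kg and a first Curosurf dose at 1 kg. Volume together with weight does, even with no product name on the form.

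**3. Would the vial record identify the arm?** There is no coded vial number to write down instead of the product, and the labels name the product. A form that records product or lot therefore shows the arm. Vial size often would too. For Curosurf, "There are two vial sizes for the study 1.5 mls and 3.0 mls"; for BLES, Sections 6.2 and 6.3 give 3 and 5 ml. Since both products have a 3 ml vial, size is informative only when it is 1.5 or 5 ml.

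**4. What do the documents leave open?** They do not list the fields on the RT's source document, say whether accountability forms count as source documents, say where completed forms are kept, or say when the Section 10 review takes place.

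**5. Illustration of size.** The shifts below are assumptions and come from nowhere in the protocol. With 44 infants per arm, one infant whose 48-hour status changes moves the difference by 1/44 = 2.3 points. The rejection rate is an exact binomial enumeration of the uncorrected two-sided 5% chi-square test, with no true effect and the Curosurf proportion raised by the shift. Base rates of 40% and 55% are the ends of the range in Section 8.1.

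| Assumed shift | Infants (shift × 44) | Rejection, base 40% | Rejection, base 55% |
|---|---|---|---|
| 0 points | 0 | 5.2% | 4.7% |
| 5 points | 2.2 | 7.5% | 7.5% |
| 10 points | 4.4 | 14.9% | 16.4% |

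**6. Two related statements in the same area.** Section 6.1 has the study Investigator calculate the weight-based dose. The volume per kilogram differs by arm, so whoever calculates the allocated dose knows the arm, yet Section 6 blinds the clinical and research teams. Section 6 also describes the RT who gives the drug as blinded, and then says that blinding this RT is not feasible.

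**The case against.** The strongest reply is that no conflict need arise in practice. Section 6 says only that the RT documents the procedure. A source document limited to time, dose number and tolerance would satisfy both Section 6 and Section 10. The accountability logs are listed apart from source documents and sit under drug storage, so the Section 10 review may not reach them. Log instructions are in a Resource Manual that is not shown, and the administration procedure in Appendix E appears only as a heading in the text available; either may already set masking and custody. A specific blinding rule would also normally prevail over a general sentence on data quality.

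Much of this stands. A reader might infer that the two rules cannot both be followed, or that following the plan necessarily shows the arm. The documents do not support that, because the form's fields are not stated. A reader might also infer a direct route to bias in the 48-hour endpoint. That is not shown either: no review time is given, so nothing establishes that clinicians would see the records before they decide on extubation. Nor does the endpoint itself leave data staff much room for judgement in coding.

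The reply does not remove the Section 10 rule. It covers all source documents without qualification, and a manual that withheld a dosing source document from the clinical team would contradict the protocol as written. Since the chart omits product and dose, the RT's forms and logs are the likely place for both to be recorded.

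**Conclusion.** The concern holds as a conflict on the face of the text, not as a demonstrated unblinding. Only the chart is masked. The dosing source document and subject accountability forms have no stated masking or access limit and probably identify the arm. Section 10 requires blinded staff to review all source documents.

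That the records identify the arm assumes that the dosing form shows product, dose or volume (with weight), and that the vial form shows product, lot or a distinguishing vial size. That the accountability forms would reach blinded staff assumes that they count as source documents or are otherwise accessible. The number of infants affected and the timing cannot be determined from the protocol, so the size of any bias is unknown; the 5- and 10-point rows are illustrations, not estimates. The protocol should be corrected, because the blind protects an endpoint that rests on a discretionary clinical act and the correction is cheap.

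**What to change.** - **Section 10 (Data Management Responsibilities):** except from review by blinded clinical and data entry staff any dosing source document that shows product, dose or volume, and the subject accountability forms.
- **Sections 6 and 6.4:** state that the unblinded RT or the pharmacy holds these records, that the pharmacy and the existing monitor check them, and that they stay closed to blinded staff until database lock or emergency unblinding.
- **eCRF:** limit the dosing page seen by blinded staff to dose number, date and time.
- **Sections 6 and 6.1:** reconcile the study Investigator's calculation of an arm-specific dose, and the description of the administering RT as blinded, with the blinding rule. The record-access change alone leaves these two open.

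The cost is a few sentences and matching wording in the Resource Manual. Pharmacy and monitoring already exist, but the forms are completed in the NICU and monitoring is planned about every 6-12 months, so the text should name who holds and checks them between monitoring dates. The small downside is that the clinical team no longer checks the dosing record.

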**Adverse Reactions**

Both study drugs have potential adverse reactions and the study staff should carefully monitor the infant for any or all of the following:

**Adverse Reactions of both Curosurf**® **and BLES**®

- Bradycardia and hypotension -during administration

**Adverse Reactions of Curosurf**®

- patent ductus arteriosus
- intraventricular hemorrhage of all grades,
- pneumonia
- sepsis
- pulmonary interstitial emphysema,
- pulmonary hemorrhage
- pneumothorax
- recurrent apnea
- retinopathy of prematurity,
- bronchopulmonary dysplasia

**Adverse Reactions of BLES**®

*Very common adverse* events occurring in10% of infants who received BLES® (bovine lipid extract surfactant), in descending order of frequency, were:

- patent ductus arteriosus
- decreased post-dose pulmonary function values,
- intraventricular hemorrhage of all grades,
- sepsis,
- retinopathy of prematurity,
- bradycardia
- severe intraventricular hemorrhage

*Common adverse events* occurring in1% and < 10% of infants who received BLES®, in descending order of frequency, were;

- pulmonary interstitial emphysema,
- periventricular leukomalacia,
- pneumothorax,
- pulmonary hemorrhage,
- endotracheal tube complications,
- necrotizing enterocolitis,
- respiratory acidosis,
- convulsions,
- hypotension,
- apnea,
- hydrocephalus
- pneumonia

.

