# Appendix D: Secondary Outcomes

1. Extubation failure (defined as in Appendix C )

2. Duration of first intubation (in hours/days)

3. Total duration of respiratory support (ventilator and nCPAP) and

Total number of days of oxygen requirement

4. Number of doses of surfactant received

5. Adverse events during or after administration of surfactant:

a) Severe airway obstruction, defined as sudden and severe desaturation < 80% with bradycardia (heart rate <100 bpm) with absence of visualization of chest movements with no response to increases in ventilator pressure or bagging for ≥3 minutes and requiring suctioning of surfactant or change of endotracheal tube (ETT)

b) Need for cardiopulmonary resuscitation

c) Pulmonary hemorrhage, defined as fresh blood in the ETT lumen associated with an increase in ventilation or oxygen requirements

d) Pulmonary air leaks (pneumothorax and/or pulmonary interstitial emphysema (PIE) on CXR)

6. Bronchopulmonary dysplasia, defined as oxygen or respiratory support requirement at 36 weeks corrected GA

7. Mortality prior to discharge

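### Section 6 says the clinical and research teams stay blinded, but the only masking it describes during instillation is a label over the syringe contents, although the volumes differ two-fold or more

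*Protocol*

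**What the plan says.** The blinding procedure is set out in the protocol, Section 6 (Study Medication/Intervention). Section 7.2 refers back to it and applies the same method to every dose.

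- **The administering RT.** Section 6 states: "As the volume and viscosity of Curosurf® and BLES® are different, blinding of the RT administering the surfactant is not feasible". Earlier in the same section, the RT who gives the drug is described as blinded.
- **Before and after dosing.** The dose is prepared away from the bedside, and "The surfactant will be drawn into a syringe and placed in a covered box". The chart entry omits product and dose, and the RT gives the infant no direct care for at least 48 hours.
- **At instillation.** "The RT will administer the surfactant with the syringe masked by a large label covering the amount of the contents". Section 6 mentions no screen, no common syringe size and no rule on who may be present.
- **Everyone else.** "The clinical and research teams will be blinded to the identity of the assigned surfactant throughout the study", except for emergency unblinding.
- **Volumes.** "The treatment dose for Curosurf® is 2.5 ml/kg (200mg/kg) for the first dose and 1.25 ml/kg (100mg/kg) for repeat doses". The comparator has a single figure, with no separate volume for repeats: "For BLES® the recommended dose is 5 ml/kg".
- **Decisions.** Section 4.1 has the RT and the physician assess readiness for extubation. Appendix B gives numeric criteria, then lets individual physicians extubate from higher settings at their discretion. Section 7.2 permits, but does not require, redosing once oxygen and radiological conditions are met.

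**The concern.** Section 6 gives volume and viscosity as the reason one person cannot be blinded, then relies on a label that hides the amount in the syringe to blind everyone else. A label does not conceal plunger travel, fluid passing down the tube or the time the instillation takes. The same cues are open to any other RT, nurse or physician standing beside the infant.

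The primary endpoint, alive and extubated at 48 hours, depends in part on a clinician's decision, and so does the need for additional doses, a secondary endpoint. The protocol also states expectations with a direction: quicker improvement and more successful extubation with Curosurf (Section 1.1), and fewer obstruction-related complications because its volume is smaller (Section 1.3). The feature that could reveal the arm is thus also a stated reason to expect a better course. If decision-makers infer the arm, the comparison can be biased while the report claims a blinded clinical team.

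**Working it through.** **1. Size of the visual cue** (volumes from Section 6)

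- First dose, BLES to Curosurf: 5 / 2.5 = 2.0.
- Repeat dose: 5 / 1.25 = 4.0, assuming BLES repeats stay at 5 ml/kg.

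Both doses are per kilogram, so the ratios hold at any weight. At an assumed 1.0 kg, the volumes are 2.5 v 5.0 ml at first dose and 1.25 v 5.0 ml at a repeat. On the same assumption there is also a cue within an infant: the Curosurf volume halves between first and repeat dose (2.5 to 1.25 ml/kg) while the BLES volume does not change.

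**2. Which safeguard covers the instillation**

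| Safeguard in Section 6 | What it hides | Hides the instillation from an onlooker? |
| --- | --- | --- |
| Preparation away from the bedside | Drawing up | No |
| Covered box | Syringe in transit | No |
| Chart entry without product or dose | Later reading of the chart | No |
| 48-hour separation | Knowledge held by that RT | No; it covers that RT only |
| Label on the syringe | Amount of contents | In part |

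**3. The plan's own sample size, as a check on the setting**

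Inputs from Section 8.1: 44 per group, type-I error 5% (taken as two-sided, since the side is not stated), control rate 40% to 55%. With p the mean of p1 and p2, the normal approximation with pooled variance under the null is

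power = Φ{ [|p2 − p1| − 1.96 √(2p(1 − p)/44)] / √([p1(1 − p1) + p2(1 − p2)]/44) }.

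The four pairs in the table (40/69.3, 45/73.9, 50/78.3, 55/82.3%) give power of 0.799, 0.799, 0.801 and 0.799. A full 30-point difference gives 0.819 at a 40% control rate and 0.880 at 55%. The stated size is reproduced and is not in dispute.

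**4. What a shift in decisions would do (illustration only)**

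Suppose the drugs do not differ, but knowledge of the arm raises the 48-hour proportion in one arm by s points. The chance of a significant result was found by enumerating every outcome of two binomial samples of 44 with the uncorrected chi-square test at two-sided 5%:

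| Base rate | s = 0 | s = 5 points | s = 10 points |
| --- | --- | --- | --- |
| 40% | 5.2% | 7.5% | 14.9% |
| 45% | 4.7% | 6.9% | 14.3% |
| 50% | 4.4% | 6.9% | 14.9% |
| 55% | 4.7% | 7.5% | 16.4% |

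The planned analysis is an adjusted logistic regression, so the chi-square test is a stand-in. The shifts are assumptions; the protocol gives no basis for choosing a value.

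**The case against.** **Appendix E.** Section 6 says the drug is given according to the administration SOP there, and that appendix is a heading without text in the version read. Syringe size, shielding or attendance could be fixed in it. This stands, and limits the claim to what Section 6 describes. It does not remove the point: Section 6 presents its list as the blinding procedure, and Section 7.2 points to Section 6.

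**Real safeguards exist, and the design is called partially double-blinded.** Both are true, and the 48-hour separation matches the primary-endpoint window. But the separation covers only one RT, and the qualifier does not help because blinding is asserted for the very teams at issue.

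**The plan does not place decision-makers at the dosing.** A reader might infer that it does. Section 6.1 says "the study staff should carefully monitor the infant for any or all of the following", and its list includes bradycardia and hypotension during administration. Appendix D defines severe airway obstruction in part as "requiring suctioning of surfactant or change of endotracheal tube (ETT"). Neither text supports that inference. The list also covers late outcomes such as retinopathy, study staff could include the administering RT, heart rate and blood pressure can be read from monitors, and Appendix D does not say who acts. Nothing says that those who later decide extubation watch the instillation. This stands: their presence is possible and not ruled out, but it is not planned.

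**Extubation and redosing follow stated criteria.** Largely true, and this limits the room for bias. The discretion in Appendix B and the permissive redosing wording in Section 7.2 leave some.

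**Syringe size and the decision shifts are not in the documents.** Correct. It cannot be said that the syringes differ in size, only that no common size is required, and the false-positive rates do not estimate bias in this trial.

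**Conclusion.** The point holds in a limited form. Section 6 contradicts itself on whether the administering RT is blinded, and it asserts blinding of the clinical and research teams that its stated procedure does not secure during instillation. The volume ratio of 2 at first dose rests on stated figures; the ratio of 4 at repeats assumes an unchanged BLES volume. That an onlooker could recognise the arm is an inference, but one that follows from the protocol's own reason for not blinding the RT.

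The stronger reading, that the team is in fact unblinded and the primary result biased, is not supported. The documents do not show who attends, how many would infer the arm, or that decisions would change. The rates of about 7-7.5% and 14-16% show only what assumed shifts of 5 and 10 points would do at 44 per arm. The weakness is worth correcting because the endpoint has a discretionary part and the correction is cheap. It is not a reason to doubt the design as a whole.

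**What to change.** In Section 6:

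1. Require one size of fully opaque syringe for both products and for all doses.
2. Shield the syringe and plunger from other bedside staff during instillation, and state that the shield is removed at once if airway care needs it.
3. Record on the dosing form whether anyone who decides extubation or redosing within 48 hours saw the instillation.
4. Reconcile the description of the administering RT as blinded with the statement that this is not feasible, and align Appendix E with the result.

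Keep the intention-to-treat primary analysis as it is. Report the number of exposed infants by arm, and treat any analysis by exposure as descriptive only. Infants should not be excluded because of a dosing emergency: that is a post-randomisation event that may differ by arm, so excluding them could create the bias the check is meant to detect.

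The cost is a paragraph in Section 6, one eCRF item, a shield at each site and slightly more set-up at dosing. No dose, volume or clinical rule changes.
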